## Abstract

**Introduction:**

Since 2013, *headspace* Denmark has been offered in specific areas to adolescents and young adults between 12 and 25 years, to promote youth mental health and wellbeing. *Headspace* provides free counselling and support, primarily delivered by trained volunteers in the *headspace* centres and provides information and knowledge about youth mental health, and *headspace* services, through community engagement. Until now, effectiveness evaluation of the Danish *headspace* centres has not been conducted.

**Methods:**

Present study consists of (1) an effectiveness evaluation designed as a propensity score matched quasi-experimental trial, where the exposed person (*n* = 1,500), in this case the young person receiving counselling sessions at *headspace*, will be matched by using propensity scores to six unexposed individuals. (2) A cost-effectiveness evaluation (3) a process evaluation with predominantly qualitative methods to investigate the implementation of key activities of *headspace,* their mechanisms of change, and interactions with contextual factors.

**Discussion:**

*headspace* centres have achieved national endorsement and are implemented in 30 municipalities in Denmark. Thus, there is a need to investigate the effectiveness of the services. Results from the evaluation can also contribute to new knowledge targeted at international youth mental health promotion initiatives. However, this evaluation is limited by selection bias since it is not possible to separate the impact of the intervention from the impact of help-seeking behaviour.

## Introduction

Increasing rates of poor mental health among adolescents and young adults is a serious, global public health concern (1, 2). About 62.5% of all mental illnesses have their onset before the age of 25 years (3) and are considered the leading cause of disability in most European countries (4). In Denmark, youth mental health is a pivotal public health challenge (5). According to the Danish Health Authorities, more than 73,000 children and adolescents (corresponding to 63 out of 1,000 youths) are living with a mental illness, which is a 39% increase over the last 10 years (6). Furthermore, national surveys on health and wellbeing in persons up to 24 years of age show that although most young people in Denmark perceive their health to be good, there is an increasing proportion of adolescents and young adults reporting mental health complaints such as high levels of stress and emotional problems (5). There is no doubt that mental health problems pose a threat to young people’s health, wellbeing, and opportunities for thriving and living fulfilling lives. Mental health problems in childhood and adolescent years are also associated with health deterioration, e.g., recurrent illness episodes and functional impairment (5), and obstruction of educational and vocational attainment (7, 8). Thus, poor mental health in youth does not only have adverse consequences for the individual but also for society in terms of loss of productivity and increased expenses to health and social services (1, 9–11).

In Denmark, the health care system is publicly funded, which means that mental health services are available to everyone, free of charge. Despite this, a gap exists between the growing group of young people with mental health complaints and those who receive sufficient support in the mental health system. Barriers for young people to access traditional mental health services include stigma towards mental health problems, long waiting lists for assessment and treatment, and lack of mental health literacy (12, 13). Investments in preventive and mental health promotion initiatives are necessary to help and support young people with mental health complaints before more severe mental health problems develop with the risk of consequently social and/or vocational marginalisation.

To address the above-mentioned challenges and to empower young people with information about mental health, and opportunities for support, the Non-Governmental Organisation, Det Sociale Netværk, has during the previous decade established 30 *headspace* centres in municipalities in all Danish Regions. The *headspace* centres provide a low threshold and easily accessible supportive place regarding mental health, to promote mental health and wellbeing in youth between 12 and 25 years. The *headspace* centres have a “soft entry” to make it as easy as possible for young people to get help to any problem they have, that may affect their mental health and wellbeing. In Denmark, the *headspace* centres are based on and branded like the Australian *headspace* model, but contextual adaptations have been made, to meet local needs (14). The *headspace* centres offer free counselling services (“*someone to talk to*”) predominantly delivered by trained adult volunteers. The volunteers work in pairs, either with another volunteer, or an employed counsellor in the *headspace* centre. In contrast to the Australian *headspace* model, mental health assessment and treatment are not provided. If the counsellor finds that the person may need, for instance, clinical treatment, the person is supported to access these services. This is referred to as bridge building in *headspace*.

The dissemination of *headspace* centres in Denmark necessitates evidence-based knowledge on whether *headspace* is an effective intervention to promote mental health and wellbeing among young people. It also necessitates knowledge on the costs and outcomes of *headspace*. An evaluation of the impact of *headspace* in Denmark on young people’s lives and a cost-consequence analysis was conducted by a consulting agency in 2019 (15). Findings showed that 94% of the youth receiving counselling in *headspace* reported feeling understood and respected. Additionally, the evaluation indicated that counselling sessions improved the wellbeing and life satisfaction of the participants. According to the Cantril’s ladder (16), there was an average of 9% improvement in life satisfaction, while the General Population - Clinical Outcomes in Routine Evaluation (CORE-GP) (17) scale showed an average 7% rise in mental wellbeing. Additionally, the proportion of people who reported feeling lonely reduced by 9% according to the Three-Item Loneliness Scale (18). However, it was emphasised that a major limitation was the lack of a comparable control group, which meant that no firm conclusions could be drawn regarding the effects of *headspace.* The analysis of cost and returns to society was based on *headspace* operating costs and scenario-based analyses where the derivative effects for the young people were estimated. Based on the evaluation, it was therefore not possible to draw any conclusion on the cost-effectiveness of *headspace* due to the short follow-up period, the lack of a control group, and the lack of register-based health care and municipal social care costs (15).

A 2022 national evaluation of headspace in Australia utilised a pre-post treatment comparison design, with regression to mean adjustments, by using the variation in outcomes measured at intake and before the second session. The results showed improvement across all outcomes: wellbeing, functioning and quality of life. In 52% of the young people the improvement was clinically significant in at least one of the outcomes (19). Findings indicated that higher session attendance was associated with greater reductions in distress, as measured by the Kessler Psychological Distress Scale (K10), and improvements in psychosocial functioning, assessed through the Social and Occupational Functioning Assessment Scale (SOFA). For instance, young people who attended two sessions showed minimal change (−0.1 K10; +0.5 SOFA), whereas those attending 3–5 or 6–9 sessions experienced greater improvements (−1.5 and −2.2 K10; +2.7 and +5 SOFA, respectively). The Australian evaluation cannot be directly compared to the Danish evaluation conducted by Rambøll, as the studies measured different outcomes using distinct methodologies. However, the two evaluations suggest that improvements are attainable, in outcomes related to youth mental health. Matthay et al. (20) emphasise that effect sizes vary based on intervention features (intensity, duration, content, and implementers) and mechanisms. Unlike Australia’s primary care-based model, staffed by health professionals and offering treatments such as cognitive behavioural therapy and medical consultations, *headspace* centres in Denmark operate as a volunteer-driven civic initiative without mental health specialists, making it a lower-intensity, non-medical intervention. Thus, smaller effect sizes than the ones identified in the Australian evaluation may be expected in this evaluation of *headspace* in Denmark. However, small effect sizes can also be important, from a mental health promotion and prevention perspective (20). Thus, more scientifically based knowledge is needed about if and how the *headspace* intervention can enhance youth mental health and wellbeing and prevent mental illness. There is also a need for documentation of the cost-effectiveness of the intervention where all relevant costs are measured. This is important to inform policymakers in deciding future investments and implementation of preventive mental health interventions like *headspace* to ensure that resources are being used properly. Moreover, there is a growing need to investigate the key activities of the Danish *headspace* intervention and to document how these can be implemented in a local context and how they might create the expected effects on youth mental health and wellbeing.

The overall aim of present evaluation is to investigate the potential effects on young individuals in the presence of *headspace* entities offering easy access and counselling for help-seeking youth, as well as the cost-effectiveness of the intervention. In addition, the aim is to investigate key activities of the *headspace* intervention utilising a process evaluation and analyse how the key activities can support the intended effects in different local contexts.

### *headspace* Denmark

The *headspace* intervention can be mapped as a complex intervention since it consists of several flexible components that interact to produce change, involves many types of stakeholders and organisations, and is expected to create multiple outcomes. To accommodate this complexity, the study is guided by the Medical Research Council (MRC) guidelines for evaluation of complex interventions (41). Consequently, the study takes a point of departure in a figurative programme theory for the *headspace* intervention (see Figure 1). The preliminary programme theory was developed for this study in collaboration with central *headspace* management and is based on internal documents in the Danish *headspace* initiative.

**Figure 1 fig1:**
[figure not shown]
Logic model of the headspace intervention. The figure provides an overview of (1) the activities in headspace; yellow activities are in direct contact with service users, whereas grey, green, orange, and blue activities primarily support the yellow activities, (2) the inputs (personnel) that are necessary to deliver the activities (3) the mechanisms by which the key activities are expected to create the intended outcomes, and (4) the expected proximal and distal outcomes. Yellow outcomes are directly related to service users, while the green and orange outcomes support the yellow proximal outcomes as indicated by the arrow.

### *headspace* centres

*headspace* Denmark consists of 30 *headspace* centres and one national chat centre. All centres offer free counselling to young people between 12 and 25 years. The *headspace* centres are staffed with one cross-centre manager (one manager serves about three *headspace* centres), two paid counsellors, volunteer counsellors, and two part-time (15 h. per week) assertive professionals employed in the local mental health services and/or social services. The *headspace* centres are located so they are accessible to young people (for instance close to public transportation). The centres furniture and decorations signal a youth-friendly atmosphere. The *headspace* centres are open 3 days a week, between 12 and 18 (12 AM to 6 PM) and the chat centre is open between 12 and 22 (12 AM to 10 PM).

Training of counsellors involves an online training program, a weekend course, and on-site training and supervision with experienced counsellors and professionals. The counselling provided to the youth is delivered in an open-minded, curious, and flexible approach, and the counsellors are guided by a person-centred approach that sets the young person’s needs at the centre of their work. Volunteering is a key principle in the *headspace* organisation, and young people seeking counselling and support are informed that most counsellors are volunteers.

Young people accessing counselling do not need to state their name or personal ID number, so their identity remains anonymous. The *headspace* centres operate under the motto “Nothing is too big or too small,” meaning that all young people in the targeted age group can access the centres. Should the young person require additional support such as a mental health assessment, specialist treatment or support from social services, the counsellors can offer support and guidance in accessing these services. In addition to counselling and bridging to other services, *headspace* centres play an active role in providing information about youth mental health, de-tabooing mental health problems among young people, as well as making *headspace* centres visible and thus accessible through community engagement and collaborations with schools, etc.

## Overall study design

The study protocol consists of three studies: an effectiveness evaluation, a cost-effectiveness evaluation, and a process evaluation, to provide a holistic and comprehensive understanding of *headspace* Denmark, to determine whether the intervention meets it objectives, to investigate the costs of the intervention to the outcomes achieved, and to analyse how the intervention is implemented to improve youth mental health. An overview of the three studies is provided in Figure 2. Appendix 1 shows a timeline of the studies.

**Figure 2 fig2:**
[figure not shown]
An overview of the three studies comprising the evaluation of headspace Denmark.

## Study 1: effectiveness evaluation

### Methods

#### Study design

The evaluation is designed as a propensity score matched quasi-experimental trial, meaning that a young person receiving counselling sessions at *headspace* will be matched by using propensity scores to six unexposed individuals (controls) based on several background characteristics with potential associations to *headspace* participation. The study will, by establishing a comparable control group, evaluate the results from the *headspace* group and measure whether *headspace* has any effect on mental wellbeing, loneliness, life satisfaction, and self-efficacy at 6 months follow-up, and measure the effects on labour market affiliation, and contact to public social and psychiatric services at 3 years follow-up.

#### Study sample

In total, 1,500 *headspace* service users are aimed for being included during the first 15 months of the study. The inclusion criteria for the intervention group are age between 12 and 25, participation in at least one counselling session in one of the physical national *headspace* centres, and willingness to give informed consent to participate in the study. Since some young people will have had one or more sessions at a *headspace* centre before the data collection begins, it is required that the first recorded measurement of young people is also their first actual session at a *headspace* centre. Young people attending the first session in *headspace* receive oral and written information about the study, from the counsellors. They are informed about the study’s purpose and procedures, including using questionnaires and register data. It is stressed that participation in the study is voluntary, and that declining to participate does not have any negative consequences for them, e.g., their right to receive counselling in *headspace.* Persons wanting to participate in the study are given a link, where they can log in to provide personal information (e.g., unique personal ID number, contact information), give informed consent and fill out questionnaires. Youth below 15 years are provided with a link to give to their parents/caregivers who need to provide consent before the person can participate in the study.

All included participants will be registered with their unique personal ID number which allows for individual-level linkage of information across nationwide registers provided by Statistics Denmark. Young people who do not want to provide their unique personal ID number cannot participate in the study. As *headspace* collects basic information on users, a supplementary analysis will be made comparing *headspace* users accepting registration on unique personal ID with *headspace* users not accepting to give their personal ID and participate in this evaluation. This comparison includes age, gender, and additional information on social and health-related problems faced by participants.

#### Procedures for matching the control group

The matching procedure must ensure that the control group is selected on significant prognostic characteristics, related to the young person contacting the *headspace* centre, which are like a participant in *headspace*. After 6 and 15 months of the 15 months inclusion period, controls are matched to the included *headspace* users using propensity score matching. Approximately 10,000 controls in total, living outside of the current *headspace* catchment area, will be matched. The repeated matching procedure is to ensure that the time lag between the *headspace* users’ survey response and the matched control can be reduced to 6 months. Table 1 presents an overview of the planned factors and registers in the matching.

**Table 1 tab1:** Variables planned to be included in the matching procedure.

Measure	Register name and provider
Psychiatric Outpatient courses Psychiatric Outpatient visits Psychiatric Hospitalisation	National Patient Register (LPR, LPR3, LPR-PSYK), The Danish Health Data Authority
Diagnosed psychiatric illness	National Patient Register (LPR), The Danish Health Data Authority
Preventive efforts to children provided by social services, which are initiated to avoid placement out of home	Statistics Denmark, Preventive efforts to children provided by social services (BUFO, BUU)
Placement out of home	Statistics Denmark, Children and youth placed out of home (BUAF)
Wellbeing in primary, short-term tertiary, and upper secondary school	Wellbeing surveys in primary, short-term tertiarty and upper seconday school. National Agency for It and Learning
Absenteeism from school	Absenteeism from school National Agency for It and Learning
National school tests, (math and Danish)	National school tests, National Agency for It and Learning Final grades for short-term tertiary and upper secondary school. (UDG), Statistics Denmark,
Parental income	Statistics Denmark (IND)
Parental employment and income transfer	Statistics Denmark (DREAM, AKM)
Parental marital status	Statistics Denmark (CIV)
Household type Parental ethnic background Sibling counts Parental civil status (diseased, divorced, etc.) Address change counts	Statistics Denmark (BEF, FTBARN, FTFORAEL)
Morbidity and health care use Parental morbidity and health care use	National Patient Register (LPR, LPR3), The Danish Health Data Authority The National Health Insurance Service Registry (SSR)
Primary health care use and chronic illness management	The National Health Insurance Service Registry (SSR)
Educational activities	Statistics Denmark (UDDA)
Delinquency and incarceration Parental delinquency and incarceration	The Danish Central Crime Register (KRAF) The Danish Central Crime Register (KRMS)
Prescription drug use	The Register of Pharmaceutical Sales (LSR)
Parental psychiatric illness, and substance use	National Patient Register (LPR) The Danish Health Data Authority
Disability services received	Handicap (HANDIC)
Neighbourhood effects, aggregated measures of: Unemployment Income Family types	Derived from above sources

Propensity scores are estimated using regularised logistic regression (11), or a low-depth random forest with *headspace* participation as a binary outcome. The matching will be done using the probability score and an optimal matching algorithm that will select the six closest matches with a caliper threshold at or below 0.25 on the log (odds) transformation of the propensity score. No replacements will be used. Missing values in predictors are handled by adding missingness indicator categories to categorical data and by replacing missing data with model-based imputations or slicing numerical variables in quantiles and then adding a categorical indicator of missingness. Matching will be carried out in two repeated batches with no overlap or cross-sample replacement. When all baseline data is collected, the matching is reiterated for the whole pool of cases and controls to ensure optimal balance on all matching parameters, at the cost of a smaller control group. The matching parameters will include all self-reported outcomes (e.g., wellbeing, loneliness) and register-based outcomes (e.g., number of hospitalizations or outpatient contacts). The statistical power obtained for numerical outcomes is above 0.98 for Cohen’s D at 0.15, even in the case of a reduction of controls to a 2:1 ratio in the final matching.

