## Discussion

This paper presents the study protocol for three studies: an effectiveness, cost-effectiveness, and process evaluation of the *headspace* intervention in Denmark. Because the *headspace* model has achieved national endorsement and is fully implemented in 30 municipalities throughout Denmark there is an urgent need for scientific knowledge about the effectiveness of the intervention. The evaluation will contribute with new, important knowledge that not only will benefit *headspace* Denmark, but also contributes with new knowledge and documentation targeted to international mental health promotion initiatives, primary and lower secondary schools, educational institutions, and municipal social initiatives.

Overall, the three studies presented in this paper will bring new knowledge about the potential contribution and impact of *headspace Denmark* as a preventive intervention and contribute with new and useful knowledge about the possibly derived effects of counselling sessions in *headspace*. The large number of participants, as well as the establishment of a matched control group and long-term follow-up, makes it possible to provide more reliable and accurate estimates compared with previous studies.

The economic evaluation will contribute new knowledge about the cost-effectiveness of *headspace* Denmark, which can be used for a more nuanced societal prioritisation of resources allocated to vulnerable young people. Finally, the process evaluation will thoroughly describe the key activities of the Danish *headspace* intervention and document how these can be implemented in a local context and how they might create the expected effects on youth mental health and wellbeing. This valuable information can in a future perspective be used to further qualify the *Danish headspace* model.

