### Methodological challenges

Despite a comprehensive study design, some methodological challenges exist. The main limitation of this study is the design—that the effectiveness evaluation of the Danish *headspac*e model is not performed as a randomised controlled trial, as it was not practically possible. The second most important limitation is difficulties in identifying a control group. We have tried to solve that by matching on failure to thrive, but we cannot identify the most important variable: help-seeking behaviour. Therefore, there is a risk that participants in the control group might have a better prognosis because they do not feel quite as bad (even though they have the same wellbeing and other match factors). There may also be a risk that participants in the *headspace* group have a better prognosis because they were able to seek and find help. There is also a risk that young people in the control group seek help from *headspace* centres after taking part in the study. Although the members of the control group live outside the catchment areas of the headspace centres, there might be a chance that some individuals contact the centres or the national chat centre during the study period. This introduces a risk of contamination, as both groups will be exposed to the intervention investigated. Young people in the control group who need help can use available social and health services, and mental health support offered in their community, but no signposting to specific organisations/services is provided in the material sent to the participants.

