A potential pitfall in the effectiveness evaluation pertains to selection bias and the dynamics of outcomes before participation in the study (33). Young people’s mental health and wellbeing may be volatile with emotional ups and downs rather than persistent with the same levels of wellbeing over time, for instance shown in a study by Tegner Anker et al. (34). Youth would primarily seek help at “mental downturns,” that is at times with high level of emotional distress, there will be a regression to the mean, that might be difficult to identify in the control, thus posing a risk that natural improvements will be interpreted as effectiveness of the *headspace* intervention. While analysing the data, differences between the groups on all baseline outcomes will be tested for statistical significance. The analyses for differences between groups will be adjusted for any baseline differences with a *p*-value below 0.05.

Participants in the *headspace* group and the control group are matched on individual-level characteristics only. At the beginning of the data collection period, there were headspace centres in 22 out of the 100 municipalities of Denmark, meaning that it was not hard to identify controls. There were headspace centres is the four largest cities of Denmark (Copenhagen, Aarhus, Odense, and Aalborg) but not in some of the other larger cities such as Silkeborg or Kolding. There could be unobserved municipality-level factors potentially affecting the treatment effect estimates, e.g., related to urban density or distance to urban centres. We have, however, seen no substantial problems for the matching algorithm to identify comparable controls on the observed factors. We would also, from a pragmatic point of view, expect important municipality-level differences to be captured by the range of individual-level matching factors used (e.g., social status).

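### Controls count as unexposed by living outside an undated *headspace* catchment that grew from 22 to 30 municipalities, and the article states no way to measure or allow for crossover over 3 years

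*Protocol article*

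**What the plan says.** All references are to the protocol article.

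- **Control definition** (Procedures for matching the control group): "Approximately 10,000 controls in total, living outside of the current" *headspace* catchment area are to be matched. No date is attached to the word *current*. On timing: "After 6 and 15 months of the 15 months inclusion period, controls are matched" to the included users.
- **Follow-up** (Study design): besides the 6-month survey outcomes, the study measures labour market affiliation and "contact to public social and psychiatric services at 3 years follow-up". The economic evaluation also uses a 3-year horizon.
- **Spread of centres**: at the start of data collection "there were headspace centres in 22 out of the 100 municipalities of Denmark" (Methodological challenges). The Discussion says the model "is fully implemented in 30 municipalities throughout Denmark".
- **Contamination** (Methodological challenges): although controls live outside the catchment areas, "there might be a chance that some individuals contact the centres or the national chat centre during the study period". The article calls this a contamination risk and goes no further.
- **Traceability** (*headspace* centres): users need give neither name nor personal ID. None of the registers listed for matching, for the 3-year outcomes or for costs records *headspace* use.
- **First contact** (Study sample): cases must be at their first actual session. No matching condition on earlier *headspace* use is stated for controls.

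**The concern.** Residence is the only stated device that makes a control unexposed. On the article's own figures that device weakens over time: some municipalities that could supply controls gained a centre, and follow-up is long enough for new centres to be used. Residence gives no protection against the national chat, and a control who moves to one of the four largest cities, all of which have centres, enters a catchment area.

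A control who uses *headspace* is still analysed as unexposed. If *headspace* works, this raises the control group towards the *headspace* group and shrinks the 3-year difference. A null or small result could then mean either no effect or dilution, and the reader would have no figure with which to tell them apart. Anonymous use makes this harder to repair afterwards: what the surveys do not ask cannot be looked up in the listed registers.

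**Working it through.** **Inputs from the article.** 22 of 100 municipalities with a centre at the start; 30 at the time of writing; 1,500 cases and 10,000 controls at 3 years; 12.5% vs 10% on a binary outcome with 83% power (Sample size). A two-sided test is stated for the survey outcomes; I assume two-sided 5% here too. The rate of crossover is not given.

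**Step 1: reproduce the stated power.** With n₁ = 1,500, p₁ = 0.125, n₂ = 10,000, p₂ = 0.10 and p̄ = (187.5 + 1,000)/11,500 = 0.1033:

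power = Φ{ [ |p₁ − p₂| − 1.96·√(p̄(1 − p̄)(1/n₁ + 1/n₂)) ] / √(p₁(1 − p₁)/n₁ + p₂(1 − p₂)/n₂) }
= Φ{ [0.025 − 1.96 × 0.00843] / 0.00905 } = Φ(0.94) = 82.6%.

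This agrees with the stated 83%, so the published figure assumes no crossover.

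**Step 2: dilution.** Let c be the share of controls who use *headspace*, assumed to receive its full effect. The control rate becomes p₂ + c(p₁ − p₂), and the difference becomes (1 − c) × 2.5 points.

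| c (assumed, all controls) | Control rate | Difference (points) | Power |
|---|---|---|---|
| 0 | 10.00% | 2.50 | 82.6% |
| 5% | 10.125% | 2.38 | 78.5% |
| 10% | 10.25% | 2.25 | 74.0% |
| 20% | 10.50% | 2.00 | 63.7% |

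With the rates the other way round (cases 10%, controls 12.5%), power is about 2 points lower throughout: 80.5% at c = 0 and 72.0% at c = 10%.

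**Step 3: what the growth in centres can explain.** Municipalities without a centre at the start: 100 − 22 = 78. Net gain: 30 − 22 = 8. Share: 8/78 = 10.3%. Assuming no closures and controls spread evenly over municipalities, c = 0.103 × u, where u is uptake among controls in those 8 areas.

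| u (assumed) | c | Power |
|---|---|---|
| 5% | 0.5% | 82.2% |
| 25% | 2.6% | 80.6% |
| 50% | 5.1% | 78.4% |
| 100% | 10.3% | 73.8% |

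At 5–25% uptake the loss is 0.4 to 2 points of power. Larger losses need moves or chat use, which the article does not quantify.

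**Step 4: the ICER.** It is the cost difference divided by the outcome difference. If both shrink by (1 − c), the ratio is unchanged. If controls' *headspace* costs go unrecorded, the intervention-cost part of the numerator is not diluted while the denominator is, and that part of the ratio moves away from zero. The net direction cannot be fixed in advance.

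**The case against.** The strongest reply is that the article already discloses contamination and that a separate statistical analysis plan, not shown, may handle it. That is fair as far as it goes. It rules out saying that crossover is certainly unmeasured; the article only does not say how it would be measured. But the control definition is a design choice made in this article. The disclosure rests on residence without noting that the area has grown, and no analysis plan can recover an exposure that was never collected.

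A reader might also infer that unexposed status is settled once, from a single address. The documents do not support that. Matching runs at 6 and 15 months, is reiterated when baseline data are complete, and is repeated before the 3-year analysis. If *current* means current at each round, some new areas are already excluded. The opening dates are not given, so 8 of 78 is a ceiling under the assumptions above. The reason given for the last repetition, however, is updated register data, not residence or exposure.

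A further reply is that 10–20% uptake among all controls is speculative, and that chat contact may not carry the benefit of counselling at a centre. Both points stand. Those rows show the range; they are not a forecast.

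**Conclusion.** The point holds as a gap in the control definition and its follow-through, with a size the documents do not establish. Crossover would pull a true 3-year effect towards zero by roughly the share of controls exposed. Expansion of centres alone probably costs little: about 0.4 to 2 points of power at 5–25% uptake in the added municipalities, and about 9 points if every control there attended. Only broader uptake, through moves or chat, would bring power down to about 74% (10% of controls) or 64% (20%). These figures assume full benefit in crossed-over controls, an even spread of controls over municipalities and no closures.

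Two stronger readings should be resisted. The growth from 22 to 30 does not by itself show that the 3-year comparison is badly underpowered; the arithmetic says otherwise. Nor does dilution drive the ICER towards zero; its direction is uncertain. The 6-month survey comparison is less exposed, since openings and moves have much less time to act.

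The change is worth making because it is cheap and because, without it, a null 3-year result could not be told apart from dilution.

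**What to change.** 1. **Date the catchment.** Define it by a list of centre opening dates, applied at each matching round including the one before the 3-year analysis.
2. **Keep the as-matched analysis as the main one** and pre-specify a 3-year sensitivity analysis restricted to controls whose municipality at matching stayed centre-free throughout their follow-up. This needs opening dates and register residence at matching. It should not redefine the main control pool, because openings after matching are later events and selecting on them could add to the municipality-level differences the article already concedes. Controls who move stay in. If time lived near a centre is also wanted, dated residence must be requested, since Table 1 lists only counts of address changes.
3. **Ask.** Add one item on *headspace* contact (centre or chat, ever and since baseline) to the control surveys still to be sent. Report the share exposed, and exclude controls with contact before baseline when matching is reiterated.

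**Cost.** A list of dates, one survey item and one further register analysis. Losing up to 8/78 of controls leaves about 9,000, and power for 12.5% vs 10% goes from 82.6% to 82.0%. The limits should be stated: the restriction does not remove chat use or moves, and the survey item sees exposure only among respondents and only to 6 months.
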